## 3. Results

A total of 557 children from 13 schools participated in the study, 298 in the intervention group (from 5 schools) and 259 in the control group (from 8 schools). As anticipated in our methodology, achieving a 1:1 ratio of participants resulted in an unequal number of schools between the intervention and control groups due to variations in class sizes. This outcome was consistent with our randomization protocol, which prioritized participant balance over school number balance.

### 3.1. Anthropometry

Table 2 shows the characteristics of the participants.

**TABLE 2 tbl-0002:** Anthropometric characteristics in the pre‐intervention situation.

	Control (*N* = 259)			Intervention (*N* = 298)			*p*‐values
	*N*	Mean (%)	SD	*N*	Mean (%)	SD	
School type	8			5			
Public	87	33.6%	n/a	121	40.6%	n/a	0.063
Partially subsidized	120	46.3%	n/a	109	36.6%	n/a	
Private	52	20.1%	n/a	68	22.8%	n/a	
Sex^∗^ (girls)	155	59.8%	n/a	152	51%	n/a	0.036^∗^
Age^∗^ (years)		8.1	1.3		7.6	1.2	0.000^∗^
Height^∗^ (cm)		133.2	9.8		130.7	8.5	0.002^∗^
Weight (kg)		31.8	9.7		30.6	8.5	0.125
Body mass index (kg/m^2^)		17.6	3.4		17.6	3.2	0.957
Weight *z*‐score							
Normal (0)	170	65.6%	n/a	176	59.1%	n/a	0.245
Overweight (+1)	47	18.2%	n/a	60	20.1%	n/a	
Obesity (+2)	42	16.2%	n/a	62	20.8	n/a	
Triponderal body index		13.2 kg/m^3^	2.2		13.5 kg/m^3^	2.1	0.129
% of body fat		21.8%	7.1		22.8%	6.8	0.092
Waist circumference (cm)		61.4 cm	10.1		59.9 cm	9.5	0.050^†^

Abbreviation: SD, standard deviation.

^†^Kruskal–Wallis.

^∗^
*p*‐value < 0.05.

Both groups are comparable in weight, BMI, TMI, weight z‐score, and body fat percentage, with slight differences in age, sex distribution, and height.

The overall rate of overweight and obesity in our sample was 37.9%. When assessing the distribution of overweight and obesity among the different schools (public, subsidized, and private), we found a significantly higher proportion of overweight and obesity in public schools than in subsidized schools and a higher proportion in subsidized schools than in private schools (*p* = 0.001, Table 3).

**TABLE 3 tbl-0003:** Percentage of overweight and obesity by type of school.

	Type of school			
	Public	Partially subsidized	Private	Total
Adequate BMI, *N* (%)	107 (51.4)	153 (66.8)	86 (71.7)	346 (62.1)
Overweight, *N* (%)	46 (22.1)	41 (17.9)	20 (16.7)	107 (19.2)
Obesity, *N* (%)	55 (26.4)	35 (15.3)	14 (11.7)	104 (18.7)
Overweight + obesity (%)	48.6%	33.2%	28.3%	37.9%
Total (N)	208	229	120	557

*Note:* Pearson chi‐square: *x*
^2^(4) = 19.1993; *p* = 0.001.

Abbreviation: BMI, body mass index.

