**Results:**

A total of 557 children from 13 schools were included (298 intervention participants from 5 schools and 259 controls from 8 schools). Significant differences in overweight and obesity prevalence were observed by school type, with the highest prevalence in public schools (48.6%), followed by partially subsidized (33.2%) and private schools (28.3%) (*p* = 0.001). Among participants with available blood samples (*n* = 237), elevated fasting glucose was detected in 21 children and hypercholesterolemia in 24 children.

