### 2.2. Participants and Randomization Process

Boys and girls aged 6–10 years (1^st^ to 4^th^ grades of primary school) from public, state‐subsidized, and private schools on the island of Gran Canaria, Canary Islands, Spain, were recruited. The selection of schools was based on convenience. After obtaining a list of schools from contacts with the local diabetic association and members of the team, the project was explained and schools were invited to participate. After obtaining the consent from several schools, the inclusion in both arms of the study was randomized with a 1:1 ratio (even though we performed cluster randomization, the aim was to have a 1:1 participant ratio, not a 1:1 classroom ratio), and the parents of the students in the aforementioned classes were invited to participate. Finally, those children whose parents consented to their participation were included. To randomize the participant schools, we employed a stratified cluster randomization approach. First, we categorized schools into three types: public, private, and subsidized. In Spain, type of school (public, subsidized, or private) is a strong indicator of socioeconomic background, as documented in previous national studies. This classification has therefore been used as a proxy for SES in the current analysis (each type of school represents a different SES, with a spectrum ranging from the lowest SES in the public schools, to the highest in the private ones [11]). Although randomization was stratified by school type (public, subsidized, and private) to account for socioeconomic differences, perfect balance between intervention and control groups was not achieved. This was due to variability in school sizes and the decision to prioritize a 1:1 ratio of participants rather than number of schools. This approach was chosen to preserve statistical power while maintaining the integrity of cluster randomization.

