### 2.5. Statistical Analysis

Sample size (286 kids in each arm of the study) was estimated using the “two independent means” approach, assuming an effect size of 0.75 BMI units (SD = 1.5), 80% power, *α* = 0.05 (two‐tailed), and an expected attrition rate of 15%. The effect size of 0.75 BMI units was selected based on a balance between clinical relevance and the practical limitations of our study. Given that our sample was limited to children who volunteered to participate, a larger sample was not feasible. Therefore, we opted for an effect size of 0.75 BMI units, which we considered both clinically meaningful in the context of pediatric obesity prevention [22, 24] and achievable within the constraints of our available sample size. Statistical analyses were performed using STATA version 14MP (StataCorp LLC, College Station, TX, USA).

Although the sample size calculation was initially performed at the individual level using a two independent means approach, we acknowledge that the cluster‐randomized design requires consideration of intracluster correlation (ICC). The absence of this adjustment may have led to an overestimation of statistical power, and this is recognized as a limitation. To appropriately account for clustering, all outcome analyses will be conducted using statistical models that consider the hierarchical structure of the data, with children nested within schools. Specifically, mixed‐effects regression models (or cluster‐robust standard errors) will be used to adjust for school‐level clustering.

In the descriptive statistical study, means, minimum and maximum values, and SD were calculated for quantitative variables. For qualitative variables, counts and proportions are presented. The 95% confidence interval for mean values and proportions was calculated. The hypothesis test for comparing proportions was used to verify the difference between proportions and the Student’s *t*‐test or Mann–Whitney test (if the distribution was not normal) was used to analyze differences between means of two samples. In the case of more than two samples, the tests applied were ANOVA or Kruskal–Wallis (non‐normal samples). Significant differences were considered when *p* < 0.05. Pearson correlation coefficient was used to evaluate the existence of correlation between average moderate/vigorous physical activity per day and BMI. Outcome assessors were blinded to school allocations to ensure unbiased evaluation of results.

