### 4.1. Obesity Prevalence and Disparities Among Schools

With regard to the evolution of overweight and obesity in Spain in the last decade, data from the COSI initiative (ALADINO in Spain) show an increase between 2011 and 2015–17, with subsequent stabilization. The PASOS study [26], conducted in 2019–2020, assessed the nutritional status of Spanish children aged 8–16 years. The results showed that 23.3% were overweight and 17.3% were obese [37], further supporting the decreasing trend observed in ALADINO. However, other studies suggest an ongoing increasing trend [38]. In any case, obesity rates remain high in our country and remain a primary area for intervention in child´s health. At 37.9%, our rate is slightly lower than those described by PASOS and ALADINO, but that is probably due to the overrepresentation of private schools in our sample.

Our findings reveal significant disparities in overweight and obesity rates among different school types, with public schools showing the highest prevalence (48.6%) compared to partially subsidized (33.2%) and private schools (28.3%). This socioeconomic gradient in obesity is consistent with previous studies in Spain and other developed countries [11, 12, 39]. The SES was a clear factor influencing overweight and obesity rates. These disparities were also present in the PASOS study, with the influence of parental education and income in overweight and obesity rates, with reported increased rates in lower SES [11]. Also, further highlighting the uneven distribution of overweight and obesity among different SES strata, the PASOS study showed that the stabilization of overweight and obesity rates described in the last years by ALADINO is at the expense of the higher socioeconomic levels.

Importantly, our results also highlight the early onset of metabolic complications in this population. We detected cases of elevated fasting blood glucose (21 cases) and hypercholesterolemia (24 cases) across both groups. Childhood obesity is associated with increased risk of type 2 diabetes, dyslipidemia, hypertension, and metabolic syndrome [2]. Longitudinal studies have found childhood obesity and cardiovascular risk factors track into adulthood, with obese children having a higher risk of becoming obese adults [40].

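### The p = 0.001 for overweight and obesity by school type treats 557 children as independent although school type varies only between 13 schools, so it overstates the evidence

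*Protocol article*

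**What the plan says.** Section 2.2 defines school type at school level: "First, we categorized schools into three types: public, private, and subsidized". Section 3 gives the numbers: "A total of 557 children from 13 schools participated in the study".

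Section 2.5 commits the outcome analyses to mixed-effects models or cluster-robust standard errors, with children nested in schools. For the descriptive comparisons it lists only ordinary tests. On proportions it says: "The hypothesis test for comparing proportions was used to verify the difference between proportions".

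Table 3 in section 3.1 cross-classifies weight status (adequate, overweight, obese) by school type and reports a Pearson chi-square of 19.1993 on 4 df, p = 0.001. The text above it reads: "we found a significantly higher proportion of overweight and obesity in public schools than in subsidized schools and a higher proportion in subsidized schools"; the second comparison is with private schools, and that one p-value closes the sentence. The abstract says "Significant differences in overweight and obesity prevalence were observed by school type", with p = 0.001. Section 4.1 opens its interpretation with "Our findings reveal significant disparities in overweight and obesity rates among different school types".

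**The concern.** A characteristic that is constant within a school can be compared only between schools. With 13 schools and three types, 13 − 3 = 10 degrees of freedom remain for judging whether types differ by more than schools of the same type do. A test on 557 independent children sets that between-school variation to zero, so its p-value is too small whenever the within-type ICC is positive.

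The article accepts this principle for its outcome analyses and names the missing ICC as a limitation, but only for sample size and power. It attaches no such caution to Table 3, whose p-value supports the main empirical message of the abstract and discussion. The physical activity comparison by centre type in section 3.3 has the same structure, with only 74 children.

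There is also a wording problem. The single p-value is an omnibus result, yet it closes a sentence that describes two steps, public to subsidized and subsidized to private.

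**Working it through.** **Inputs.** Table 3 counts, in the order public / subsidized / private: adequate BMI 107 / 153 / 86; overweight 46 / 41 / 20; obesity 55 / 35 / 14; column totals 208 / 229 / 120. Overweight plus obesity: 101 / 76 / 34, or 48.6%, 33.2% and 28.3%. There are 13 schools (section 3), so the mean size is 557/13 = 42.85. Neither the ICC nor the number of schools per type is given. The ICC is therefore assumed at 0.01 to 0.05; the relevant quantity is the residual ICC within school type.

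**Step 1: reproduce the printed figure.** Expected count = row total × column total / 557 (for example, adequate BMI in public schools: 346 × 208 / 557 = 129.2). Summing (observed − expected)² / expected over nine cells gives 19.199 on 4 df, p = 0.0007. This matches the printed 19.1993 and rounds to 0.001, so no clustering adjustment was made.

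**Step 2: related tests, still ignoring clustering.**
- Overweight plus obesity yes/no by type (2×3): chi-square 16.87 on 2 df, p = 0.0002.
- Linear trend with scores 0, 1, 2: chi-square 15.33 on 1 df, p = 0.00009.
- Public v subsidized (101/208 v 76/229): 10.69, p = 0.001.
- Public v private (101/208 v 34/120): 12.85, p = 0.0003.
- Subsidized v private (76/229 v 34/120): 0.86, p = 0.35.

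**Step 3: allow for clustering.** Because type is constant within school, the full design effect applies: D = 1 + (42.85 − 1) × ICC. Each chi-square is divided by D. It is then referred to the chi-square distribution, or divided by its own df and referred to F with 10 denominator df. The trend uses t = √(15.33/D) on 13 − 2 = 11 df.

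Example at ICC 0.02: D = 1 + 41.85 × 0.02 = 1.84.
- 3×3: 19.199/1.837 = 10.45, p = 0.033 on chi-square(4); 10.45/4 = 2.61 on F(4,10), p = 0.099.
- 2×3: 16.868/1.837/2 = 4.59 on F(2,10), p = 0.038.
- Trend: √(15.333/1.837) = 2.89 on 11 df, p = 0.015.

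| Assumed ICC | D | 3×3, chi-square(4) | 3×3, F(4,10) | 2×3, chi-square(2) | 2×3, F(2,10) | Trend, t(11) |
|---|---|---|---|---|---|---|
| 0.01 | 1.42 | 0.009 | 0.054 | 0.003 | 0.020 | 0.007 |
| 0.02 | 1.84 | 0.033 | 0.099 | 0.010 | 0.038 | 0.015 |
| 0.03 | 2.26 | 0.075 | 0.15 | 0.024 | 0.061 | 0.024 |
| 0.05 | 3.09 | 0.18 | 0.26 | 0.065 | 0.11 | 0.048 |

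**Step 4: where 0.05 is crossed.** Dividing each statistic by its 5% critical value gives the largest tolerable D, and (D − 1)/41.85 gives the ICC. The results are about 0.009 for 3×3 on F(4,10), 0.024 for 3×3 on chi-square, 0.025 for 2×3 on F(2,10), and 0.043 for 2×3 on chi-square. The trend is still at 0.048 when the ICC is 0.05, and at 0.113 when it is 0.10.

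Equal school sizes are assumed. With a coefficient of variation of 0.5 in school size, the p-values are larger; for example, 3×3 on chi-square at ICC 0.02 becomes 0.053.

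**The case against.** The strongest reply is that the gradient may well be real and may survive a correct test. Section 2.2 fixes an order in advance, from lowest socioeconomic status in public schools to highest in private ones, and a 1-df trend in that order stays below 0.05 at every ICC tabulated. This stands as a reason not to call the result null. It does not rescue the printed p-value, which comes from a 4-df test on children, and section 2.5 names no trend test.

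A reader might infer from the table that clustering removes the significance. The documents do not support that: they give neither the ICC nor the number of schools per type, and the crossing point moves from about 0.009 to above 0.05 depending on the test.

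A reader might also take section 3.1 to claim significance for both steps of the gradient. The word for significance is attached to public v subsidized only, so this is an ambiguity caused by where the p-value sits, not a plain false claim.

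Finally, a reader might infer that the same defect undermines the argument in section 4 that the arms are comparable. It largely does not. That argument rests on non-significant p-values, which a clustering adjustment would normally raise. Whether Tables 2 and 4 should carry p-values at all is a reporting preference.

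It also stands that this is a baseline descriptive result. Adjustment for school type in the outcome models is justified in section 2.5 by its known association with obesity and by imbalance between arms, not by this p-value.

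**Conclusion.** The concern holds as a statement about the reported test. The p = 0.001 in Table 3, repeated in the abstract and carried into section 4.1, uses the child as the unit for a factor that varies between 13 schools, and so overstates the evidence. Significance is not established by that test, and it is not shown to be absent.

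Across assumed residual ICCs of 0.01 to 0.05, defensible versions of the test give p-values from 0.003 to 0.26. These figures rest on the assumed ICCs, equal school sizes and a simple design-effect correction; only school-level data can settle the matter. Subsidized v private is unconvincing (p = 0.35) before any allowance for clustering.

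The prevalences of 48.6%, 33.2% and 28.3% stand as description, and the planned outcome analyses, which do provide for clustering, are not in question.

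**What to change.** 1. Re-run Table 3 and the centre-type physical activity comparison in section 3.3 with school as a random effect, or with school-level summaries as the data, using small-sample degrees of freedom.
2. Report the ICC and the number of schools of each type.
3. Give the pairwise contrasts separately, and reword the sentence in section 3.1 so that p = 0.001 does not appear to cover subsidized v private.
4. If the re-analysis is not done, or the adjusted test is not significant, present the gradient descriptively and remove the significance claim from the abstract and section 4.1.

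The cost is a re-analysis of data already collected and some rewording. The downside is that the headline p-value becomes less favourable.

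### Section 3.1 attaches p = 0.001 to public > subsidized > private, but that p is the overall 4-df test of Table 3; tested directly, subsidized v private gives p = 0.35

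*Protocol article*

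**What the plan says.** The sentence in section 3.1 makes two ordered comparisons of combined overweight and obesity. The first reads "we found a significantly higher proportion of overweight and obesity in public schools than in subsidized schools". The second, "a higher proportion in subsidized schools than in private schools", follows directly and carries the only p-value in the sentence, p = 0.001, with a reference to Table 3.

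The note under Table 3 identifies the test as a Pearson chi-square and prints "2^(4) = 19.1993; *p* = 0.001". Four degrees of freedom correspond to the full cross-tabulation of three weight categories by three school types. No pairwise test and no trend test is reported for these data.

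Section 2.5 sets the threshold: "Significant differences were considered when *p* < 0.05". For proportions it says "The hypothesis test for comparing proportions was used to verify the difference between proportions".

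Section 4.1 repeats the three percentages (48.6%, 33.2%, 28.3%) as disparities among school types and adds: "This socioeconomic gradient in obesity is consistent with previous studies in Spain and other developed countries". Section 2.2 treats each school type as a different socioeconomic level, lowest in public and highest in private schools.

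**The concern.** A p-value placed at the end of a sentence with two ordered comparisons will be read as supporting both. This one can support neither by itself. Its null hypothesis is that the distribution over adequate BMI, overweight and obesity is the same in all three school types. It can be rejected because a single school type differs, and it takes no account of order. It is also not a test of the combined prevalence that the sentence quotes.

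The result is the main baseline finding and is discussed in socioeconomic terms. School type also serves as the socioeconomic proxy in the planned outcome models (section 2.2 and the end of section 2.5). A reader could take from section 3.1 that these data separate all three levels, including the upper two, at p = 0.001. The point does not depend on clustering: it holds even if all 557 children are treated as independent, which is the case most favourable to the article.

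**Working it through.** **Inputs (Table 3).** Adequate BMI / overweight / obesity:
- public 107 / 46 / 55 (N = 208)
- subsidized 153 / 41 / 35 (N = 229)
- private 86 / 20 / 14 (N = 120)

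Overweight and obesity combined: 101/208 = 48.6%, 76/229 = 33.2%, 34/120 = 28.3%.

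**Step 1: reproduce the printed figure.** The Pearson chi-square on the 3 x 3 counts is the sum of (observed - expected)²/expected, with expected = row total x column total / 557. It gives 19.1993 on 4 df, p = 0.0007, which rounds to the printed 0.001. This confirms that the p belongs to the whole table.

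**Step 2: overall test of the quantity quoted.** Collapsing to combined overweight and obesity (yes/no) by school type gives chi-square = 16.87 on 2 df, p = 0.0002.

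**Step 3: each step tested directly.** The difference is p1 - p2, its 95% CI uses the unpooled standard error, and the p-value is the 1-df Pearson test without continuity correction.

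*Subsidized v private*
- Difference: 0.3319 - 0.2833 = 0.0485, or 4.9 points.
- Unpooled SE: √(0.3319 x 0.6681/229 + 0.2833 x 0.7167/120) = 0.0516.
- 95% CI: 0.0485 ± 1.96 x 0.0516, or -5.3 to 15.0 points.
- Pooled proportion: 110/349 = 0.3152.
- Pooled SE: √(0.3152 x 0.6848 x (1/229 + 1/120)) = 0.0524.
- z = 0.927, chi-square = 0.860, **p = 0.35**.

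Other versions of this test agree: Fisher 0.40, continuity-corrected 0.42, three categories on 2 df 0.58, obesity alone 0.36.

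| Comparison | Difference (points) | 95% CI | Chi-square (1 df) | p |
|---|---|---|---|---|
| Public v subsidized | 15.4 | 6.2 to 24.5 | 10.69 | 0.0011 |
| Subsidized v private | 4.9 | -5.3 to 15.0 | 0.86 | 0.35 |
| Public v private | 20.2 | 9.7 to 30.8 | 12.85 | 0.0003 |

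**Step 4: trend.** Cochran-Armitage test with scores 0, 1, 2 and overall proportion 211/557 = 0.3788.
- Numerator: (76 - 229 x 0.3788) + 2 x (34 - 120 x 0.3788) = -33.66.
- Variance: 0.3788 x 0.6212 x (709 - 469²/557) = 73.9.
- z = -3.92, chi-square = 15.33, p = 0.00009.
- Departure from a linear trend: 16.87 - 15.33 = 1.54 on 1 df, p = 0.22.

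**Step 5: sensitivity to clustering.** The article gives no intracluster correlation, so 0.01 to 0.05 is assumed here. With 557/13 = 42.8 children per school on average, the design effect 1 + (42.8 - 1) x ICC is 1.4 to 3.1. Dividing each chi-square by it gives the following.

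| Test | p at ICC 0.01 | p at ICC 0.05 |
|---|---|---|
| 4-df test of Table 3 | 0.009 | 0.18 |
| 2-df test of combined prevalence | 0.003 | 0.065 |
| Linear trend | 0.001 | 0.026 |
| Public v subsidized | 0.006 | 0.063 |
| Subsidized v private | 0.44 | 0.60 |

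This is a rough correction that assumes equal school sizes.

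**The case against.** The sentence has a more charitable reading. The word for statistical significance stands only before public v subsidized, and that step holds on its own at individual level (p = 0.0011). The second clause says only that the proportion was higher, which is true of the sample percentages. The note to Table 3 discloses the statistic and its degrees of freedom. All of this is correct and limits the fault to the placement of one p-value. It does not remove the fault, because the p closes the whole sentence and follows the step it supports least.

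Three stronger readings are tempting, and the document does not support them.

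- A reader might infer that no socioeconomic gradient is shown. A gradient over ordered groups is usually judged by a trend test, and the trend on these counts is clear at individual level (p = 0.00009) with no evidence against linearity (p = 0.22). A trend does not establish each step, but the word gradient in section 4.1 can be supported.
- A reader might infer that the data show public schools against the other two types, with those two alike. An interval from -5.3 to 15.0 points does not show equality, and the counts fit a linear trend.
- A reader might infer that the abstract is wrong in the same way. It attaches p = 0.001 to differences by school type overall and then lists the percentages. The 2-df test of combined prevalence supports that claim more strongly than the printed p. Section 4.1 likewise speaks of disparities among school types overall.

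It is also fair that this is a descriptive baseline comparison. No sample size or planned model depends on it, and the outcome models adjust for school type whatever this step shows.

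**Conclusion.** The point holds for section 3.1. The printed p = 0.001 is the 4-df overall test of Table 3 and tests neither of the two steps to which it is attached. On the same counts the first step has direct support (15.4 points, p = 0.001). The second does not: 4.9 points, p = 0.35 against the article's threshold of 0.05. The overall association and a linear trend are both supported at individual level.

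These figures treat children as independent. Under the assumed intracluster correlations the subsidized v private p only rises, so that conclusion is unaffected. The public v subsidized step is less secure, since its p would lie between 0.006 and 0.063. It should not be restated as established without a remark on clustering. The consequence is limited to how the baseline finding is reported and read.

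**What to change.** In section 3.1:

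1. Label p = 0.001 as the test of overall association between weight status and school type, and detach it from the ordered statement.
2. Report the three pairwise differences in combined overweight and obesity with 95% confidence intervals.
3. State that subsidized and private schools were not shown to differ, and give the interval so that the statement is not read as equality.
4. Compute all of these allowing for clustering in the 13 schools, or state plainly that they ignore it.

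In section 4.1, if the word gradient is kept, support it with a named trend test handled in the same way. The abstract needs no change on this ground.

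The unadjusted results follow from counts already printed in Table 3. The clustered versions need the school identifiers in the trial data and one further run. The only downside is a slightly weaker statement of the baseline result.
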